**Methods:**

This study is a randomized controlled clinical trial involving 44 participants, who are randomly allocated at a 1:1 ratio to either the FSN group or the medication group. Participants in the FSN group receive FSN treatment twice weekly for 4 weeks, while those in the medication group are administered 5 mg oral flunarizine hydrochloride capsules nightly for the same duration. Both groups are followed up for 3 months post-treatment. The primary outcome is the change in monthly migraine days (MMDs). From baseline after 4 weeks of treatment. Secondary outcome measures including the Migraine-Specific Quality of Life (MSQOL) score, headache diary records, Migraine Disability Assessment (MIDAS), Visual Analog Scale (VAS) scores and near-infrared spectroscopy (NIRS) are also used to validate clinical efficacy.

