### Study setting

2.2

Participants are recruited from the acupuncture outpatient clinic and neurology outpatient clinic of Guangdong Provincial Hospital of Traditional Chinese Medicine. Eligible participants who provide consent are randomly assigned in a 1:1 ratio to receive either FSN treatment (*n* = 22) or pharmacological treatment (*n* = 22) for 4 weeks. Outcome measures are assessed for all participants at baseline, on day 28 after the initiation of intervention, and on days 28, 56, 84, 112, 140 and 168 after treatment completion. Additionally, NIRS measurements are performed for participants in the FSN group during the 1st, 3rd, 5th, and 7th treatment sessions within the therapeutic cycle.

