### Sample size calculation

2.4

This study is an exploratory investigation, with the primary outcome measure defined as the reduction in the monthly migraine days (MMD) from baseline after 4 weeks of treatment. As a novel acupuncture technique, Fu’s Subcutaneous Needling (FSN) inevitably lacks high-quality randomized controlled trials (RCTs) to inform sample size estimation. Therefore, reference is made to an internationally rigorous RCT on acupuncture for migraine without aura (23), and the sample size is estimated based on this study, combined with clinical FSN practice and the current study design. The hypothesis posited comparable effect sizes between the two interventions (FSN group and flunarizine hydrochloride group) in this trial and those observed in the prior study’s acupuncture and flunarizine hydrochloride groups. The referenced study reported that after 4 weeks of treatment, the MMD in the acupuncture group decreased by 4.1 ± 3.5 from baseline, while the MMD in the flunarizine hydrochloride group decreased by 1.9 ± 2.3 from baseline. To verify whether the efficacy of FSN is at least not inferior to that of flunarizine hydrochloride, a non-inferiority test is employed. Based on previous research (24), the most commonly selected non-inferiority margin for Monthly Migraine Days (MMD) in migraine studies is 1. The calculation is performed using the Non-Inferiority Tests for the Difference Between Two Means in PASS 15.0 software. With *α* = 0.05 (two-sided), power (1−*β*) = 0.9, and an anticipated 25%dropout rate, a total of 44 participants (22 per group, 1:1 ratio) are required to detect a statistically significant difference in MMD changes between the two groups.

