### Primary outcome

4.1

The change from baseline to the end of treatment (Day 28) in monthly migraine days (MMDs).

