### Secondary outcomes

4.2

Migraine-Specific Quality of Life (MSQOL) scores, including three dimensions: functional limitations (the degree to which migraines limit daily activities), dysfunction (the avoidance of certain activities due to the concern of migraine attacks), and emotional impact (the effect of migraines on mood), assessed via 14 items on a 6-point scale (0–5). Scores are calculated for each dimension.Headache diaries, recording daily migraine episodes, including presence/absence of headache, frequency, average duration, and use of acute analgesics (if taken, drug name, dosage, and frequency were documented). The reduction rate in rescue medication use was extracted as an independent outcome measure, calculated as the percentage decrease in monthly medication frequency and dosage from baseline to the end of treatment and throughout the follow-up period.Migraine Disability Assessment (MIDAS): This score evaluates migraine-related disability through five items (including the number of days that work, household chores, and social/leisure activities are affected by migraine; the score ranges from 0 to 270, with higher scores indicating greater disability).The difference in Visual Analog Scale (VAS) scores from baseline at week 4 of treatment.

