### Follow-up and recurrence assessment

4.4

Outcome measures are assessed at baseline (Day 0), at the end of treatment (Day 28), and during the post-treatment follow-up period (Days 28, 56, 84, 112, 140, and 168) to monitor the long-term durability of efficacy and the recurrence of symptoms.

Recurrence is defined as a return of monthly migraine days (MMD) to ≥80% of the baseline level during the follow-up period, as recorded in headache diaries. In the event of recurrence, management included referral for clinical follow-up (e.g., re-evaluation in a neurology outpatient clinic) and documentation of acute medication use (e.g., ibuprofen), without re-intervention to assess the natural persistence of treatment effects. Recurrence events are analyzed as a secondary endpoint.

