## Statistical analysis

6

Statistical analyses are conducted using SPSS 25. All tests employ two-sided comparisons, with statistical significance defined as *p* < 0.05.

Normally distributed continuous variables are presented as mean ± standard deviation (SD), whereas non-normally distributed variables are reported as median and inter-quartile range (IQR). Categorical variables appear as frequency and percentage (proportions).

For the MMD, MSQOL, MIDAS and VAS scale scores, between-group differences in changes from baseline to 4 weeks post-treatment are analyzed using either the independent *t*-test or Mann–Whitney U test, as appropriate. Intra-group comparisons between baseline and 4-week post-treatment measurements are conducted using paired *t*-test or Wilcoxon signed-rank test. Given the repeated measurements of MMD and the scale scores, repeated-measures analysis of variance (ANOVA) is additionally employed for supplementary analysis. For near-infrared spectroscopy (NIRS)-derived oxygen saturation levels, analyzed for within-group differences before and after treatment using paired *t*-test.

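### Section 6 places the tests four weeks after treatment, but the primary outcome is at end of treatment; the abstract's follow-up length also conflicts with the visit schedule

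*Protocol article*

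**What the plan says.** **Primary time point.** Section 4.1 of the protocol article defines the primary outcome as "The change from baseline to the end of treatment (Day 28) in monthly migraine days (MMDs". Section 2.4 sizes the trial on the "reduction in the monthly migraine days (MMD) from baseline after 4 weeks of treatment", and the abstract agrees. Section 4.2 puts the VAS outcome at the same point: "The difference in Visual Analog Scale (VAS) scores from baseline at week 4 of treatment". The same section describes MSQOL and MIDAS without naming a visit for comparing the groups.

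**Analysis time point.** For MMD, MSQOL, MIDAS and VAS, section 6 says that "between-group differences in changes from baseline to 4 weeks post-treatment are analyzed". It uses the phrase again for the within-group tests: "Intra-group comparisons between baseline and 4-week post-treatment measurements are conducted".

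**Visit schedule.** Section 2.2 lists one assessment 28 days after the intervention starts and further ones "on days 28, 56, 84, 112, 140 and 168 after treatment completion". Section 4.4 likewise lists an end-of-treatment assessment and then assessments "during the post-treatment follow-up period (Days 28, 56, 84, 112, 140, and 168". Table 1 has a Day 28 column under treatment and another under follow-up.

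**Follow-up length.** The abstract says: "Both groups are followed up for 3 months post-treatment".

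**The concern.** The endpoint definition and the analysis section give different time points for the same outcome. The one in section 6 coincides with a real scheduled visit at which MMD is recorded, so an analyst who followed section 6 to the letter could carry out the wrong comparison without noticing.

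The two visits answer different questions. If MMD counts the preceding four weeks (an assumption; the article does not state the counting window), end of treatment measures the effect during treatment, and the visit 28 days later measures how far the effect persists in the first four weeks off treatment. The planning figures in section 2.4, reductions of 4.1 ± 3.5 and 1.9 ± 2.3 days, are for four weeks of treatment. They say nothing about power at the later visit.

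The follow-up length matters because section 4.4 counts recurrence over the follow-up period as a secondary endpoint. A shorter or longer period changes how long events can be observed.

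**Working it through.** **1. Which study day each statement names.** Treatment lasts 4 weeks, that is 4 × 7 = 28 days.

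| Source | Time point as stated | Study day, counted from start of treatment |
|---|---|---|
| Section 4.1, primary outcome | End of treatment | 28 |
| Section 2.4, sample size basis | After four weeks on treatment | 28 |
| Section 4.2, VAS | Week 4 of treatment | 28 |
| Section 4.2, MSQOL and MIDAS | None given | – |
| Section 6, between- and within-group tests | Four weeks post-treatment, read literally | 28 + 28 = 56 |
| Sections 2.2 and 4.4, first follow-up visit | 28 days after treatment completion | 28 + 28 = 56 |

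The literal reading of section 6 differs from section 4.1 by 56 − 28 = 28 days and falls exactly on the first follow-up visit.

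**2. Does usage elsewhere settle the meaning of post-treatment?** No. The abstract and section 4.4 use the term for the time after the course has ended, which supports study day 56. The NIRS procedure (section 4.3.1.1) uses it for a recording made straight after needle insertion, within a session. The introduction uses it for results following an intervention. The term is not used uniformly, so study day 56 is the literal reading but not the only possible one.

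**3. Does another passage resolve it, outcome by outcome?** For MMD, section 4.1 does, and for VAS, section 4.2 does, if a formal outcome definition takes precedence over a sentence that lists tests. For MSQOL and MIDAS there is no such definition, and section 6 is the only statement of the visit. The repeated-measures ANOVA in section 6 is supplementary and does not identify a primary visit.

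**4. Follow-up length.** The stated figure is 3 months after treatment, about 3 × 30.44 = 91 days. The schedule does not reproduce it:
- Last visit 168 days after treatment: 168 / 7 = 24 weeks; 168 / 30.44 = 5.5 months.
- If Day 168 were instead counted from the start of treatment, which section 2.2 rules out: 168 − 28 = 140 days; 140 / 30.44 = 4.6 months.
- The visit nearest to 3 months is Day 84: 84 / 30.44 = 2.8 months. Stopping there leaves three follow-up visits (Days 28, 56, 84) out of six.

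No way of counting makes 168 days equal to 3 months.

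**The case against.** The strongest reply is that the primary time point is fixed consistently wherever it is formally defined: the abstract, section 2.4 and section 4.1 all give end of treatment. Section 6 lists tests for four outcomes in one sentence, and its phrase is most plausibly loose English for the end of the four-week course. This largely stands for MMD and VAS. It does not help MSQOL and MIDAS, and the phrase appears twice, so it is not an isolated slip.

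A reader might go further and infer that the primary analysis has in fact been moved to study day 56. The documents do not support that: the term is also used loosely elsewhere, and the formal definition points to end of treatment.

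A reader might also infer that two visits labelled Day 28 leave the endpoint undefined and open to choice after the data are seen. That too goes beyond the text. Sections 2.2 and 4.4 state the origin of each count, Table 1 separates the two under different headers, and the primary outcome is named. Clearer labels would help, but the labels alone are not an error.

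On follow-up, the conflict is one abstract sentence against three consistent operative places, and section 4.4, which defines recurrence, itself lists all six visits. That makes it minor, though still a contradiction. Nor does the schedule conflict with the study period. A participant is on study for 28 + 168 = 196 days, but section 2.1 gives only overall dates (April 2025 to April 2026) and no recruitment window, so no infeasibility follows.

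**Conclusion.** The point holds as a contradiction in wording that should be removed before any comparison is run. As written, section 6 puts the tests 28 days later than the primary outcome, the sample size basis and the VAS outcome. End of treatment is very probably what is meant for MMD and VAS. For MSQOL and MIDAS that is an inference, because no other statement fixes the visit. The practical consequence, an off-treatment comparison in place of an on-treatment one, arises only if section 6 is followed literally.

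The follow-up discrepancy, 3 months against 168 days (24 weeks, about 5.5 months), is real under any counting. It bears on the recurrence endpoint and not on the primary outcome. Neither part changes the planned 44 participants.

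**What to change.** In section 6, replace the time point in both sentences (between-group and within-group) with *end of treatment (Day 28 after the start of treatment)*. If a different visit is intended for MSQOL or MIDAS, state it in section 4.2 and list those outcomes separately in section 6.

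Preferably, label visits so that the two Day 28 assessments cannot be confused, for example by study day: 28 for end of treatment, then 56, 84, 112, 140, 168 and 196 for the six follow-up visits, if the existing schedule is kept.

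Reconcile the follow-up length in the abstract with sections 2.2 and 4.4 and Table 1. The weight of the text favours 168 days, but the authors must confirm which is intended, and the period over which recurrence is counted should match.

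The cost is a few words and table labels. If the existing schedule stands, there is no change to the number of participants, the visits or the data collected.

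### The non-inferiority margin is a difference in mean migraine days, but the primary comparison may be made by a rank test with no margin attached

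*Protocol article*

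**What the plan says.** The primary outcome (protocol article, section 4.1) is the change in MMD from baseline to Day 28. Non-inferiority of FSN to flunarizine is the stated hypothesis in both the Introduction and the Conclusion.

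Section 2.4 says that "a non-inferiority test is employed" and takes its margin from the statement that "the most commonly selected non-inferiority margin for Monthly Migraine Days (MMD) in migraine studies is 1". The calculation uses "Non-Inferiority Tests for the Difference Between Two Means in PASS 15.0 software". Its inputs are that "the MMD in the acupuncture group decreased by 4.1 ± 3.5 from baseline" and that "the MMD in the flunarizine hydrochloride group decreased by 1.9 ± 2.3 from baseline". Alpha is 0.05 two-sided, power 0.9 and dropout 25%, giving 22 per group.

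Section 6 compares changes in MMD, and in three other scores, between groups by an independent t-test or a "Mann–Whitney U test, as appropriate". All tests are two-sided at p < 0.05. The section gives no rule for choosing between the two tests. It mentions no margin, shifted null or confidence interval for either of them.

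**The concern.** The margin and the sample size are statements about a difference between two means, in days. A Mann–Whitney U statistic or its p-value is not in days and cannot be set against 1 day. A rank procedure can be given a margin in two ways: add 1 day to one arm before ranking, or compare a Hodges–Lehmann interval with 1 day. Both answer the question about means only if the two distributions differ by a pure shift. The protocol builds in neither, and its planning SDs differ by a factor of 3.5/2.3 = 1.5.

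If the rank branch is taken, the primary conclusion may rest on a quantity for which the trial was not sized. When unequal spread comes with skew, equal means no longer imply that neither arm tends to rank higher. The chance of declaring non-inferiority when FSN is truly 1 day worse can then move away from its nominal level, in either direction.

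**Working it through.** **1. The scale of the plan's own figure.** Inputs from section 2.4: expected advantage 4.1 − 1.9 = 2.2 days, margin 1 day, SDs 3.5 and 2.3.

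- Pooled SD = √((3.5² + 2.3²)/2) = √((12.25 + 5.29)/2) = √8.77 = 2.961.
- Distance from the margin = 2.2 + 1 = 3.2 days.
- n per group ≈ 2 × 8.77 × (z for alpha + z for power)² / 3.2².
- One-sided alpha 0.05: 17.54 × (1.645 + 1.282)² / 10.24 = 14.7, so 15; the t-test calculation gives 16. Then 16/0.75 = 21.3, so 22 per group and 44 in total, which matches the plan.
- One-sided alpha 0.025, equivalent to the stated two-sided 0.05: 18 per group by the normal formula (24 after dropout) or 20 by the t-test (27 after dropout). Neither gives 44. That mismatch is a separate matter.

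The 44 is therefore reproduced by a calculation wholly on the mean-difference scale.

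**2. The rank test as written.** With normal data, SDs 3.5 and 2.3, and FSN truly 1 day worse, a two-sided Mann–Whitney test of no difference (2,000 simulated trials per case) is non-significant in 84.5% of trials with 16 per group and 81.3% with 22. A non-significant result therefore cannot be read as non-inferiority.

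**3. The rank test given its best chance.** Suppose 1 day is added to the FSN reductions before ranking, and the test is one-sided at 2.5%. The true mean difference is exactly 1 day against FSN, with SDs 3.5 and 2.3. There are 16 per group (22 × 0.75 = 16.5) or 22 per group, and 4,000 simulated trials per case. The skewed shapes are assumptions. Positive values are reductions in MMD, so negative skew means a long tail towards little benefit or worsening.

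| Assumed shape | Shifted Mann–Whitney, 16 / 22 per group | Welch, 16 / 22 per group |
|---|---|---|
| Normal | 2.3% / 2.5% | about 2.3–2.6% |
| Skewness +1.5 | 1.1% / 0.6% | 1.5% / 1.5% |
| Skewness −0.75 | 4.2% / 4.4% | not computed |
| Skewness −1.5 | 7.1% / 7.9% | 3.7% / 3.2% |

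The simulation standard error is √(0.025 × 0.975/4000) = 0.25 percentage points at 2.5%, and √(0.079 × 0.921/4000) = 0.43 points at 7.9%.

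- Rounding to whole days leaves the −1.5 pattern unchanged: 7.0% / 7.9% for the rank test and 3.9% / 3.6% for Welch.
- With equal spread (SD 2.96 in both arms), normal or skewed, the shifted rank test gives 2.1% to 2.6%. The drift therefore needs unequal spread as well as skew.
- A stronger skew (gamma shape 1.5, skewness 2/√1.5 = 1.63), placed in both arms or in FSN only, widens the range to 0.4–10.7% for the rank test and 1.0–4.7% for Welch.

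**4. Why the direction matters.** With negative skew the median reduction lies above the mean, and the gap grows with the SD. The FSN arm has the larger SD, so it ranks better than its mean warrants. Positive skew reverses this and makes the rank test conservative.

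**The case against.** Four objections carry weight.

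First, a reader might infer that a 1-day margin has no meaning for a rank method. That goes too far. Under a location shift, shifted data or a Hodges–Lehmann interval gives a legitimate test in days. What stands is that the protocol provides for neither, and its SDs make the model doubtful.

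Second, a reader might infer that the rank test fails to hold its error rate in general. The documents do not support this. The rate is held with normal data even at SDs of 3.5 and 2.3, is held with skew when spreads are equal, and is conservative with positive skew. Inflation needs unequal spread and negative skew together, and the documents give no shape for MMD change.

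Third, nothing shows that the rank branch would be used. If a Shapiro–Wilk check made the choice, which is itself an assumption, it would send roughly 71–92% of trials to the rank test at skewness ±1.5. At ±0.75 it would send 27–36%, or 36–49% with whole-day rounding. The protocol leaves the trigger open.

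Fourth, section 6 applies the margin in neither branch, so the missing decision rule is the wider fault. That is true, and one sentence can repair both. But a margin rule added while the Mann–Whitney option stayed would still leave one branch off the margin's scale.

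The trial also calls itself exploratory, and the choice between tests is often detailed in an analysis plan that is not shown. This lowers the weight of the point. It does not remove it, because section 6 states the rank option rather than staying silent.

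**Conclusion.** The point holds in limited form. Section 2.4 puts the margin and the sample size on the difference in mean MMD change, and section 6 allows the primary comparison to leave that scale through an unspecified choice. That mismatch is in the text and needs no assumption.

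The effect on the error rate is conditional. Taking 2.5% one-sided as nominal (half the stated two-sided 0.05), the planning SDs and the assumed skews, a margin-shifted rank test passes a treatment exactly 1 day worse about 0.6–1% of the time at skewness +1.5, 4–4.5% at −0.75 and 7–8% at −1.5. The last is about three times nominal (7.1/2.5 = 2.8; 7.9/2.5 = 3.2). Welch, at about 1.5% to 3.7% over skewness +1.5 to −1.5, stays closer to nominal but is not exact. The point should be corrected before analysis, but it does not invalidate the design.

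**What to change.** In section 6, state that the primary analysis is the between-group difference in mean MMD change from baseline to Day 28, with an unequal-variance (Welch) 95% confidence interval compared with the 1-day margin, whatever a normality check shows. Keep the Mann–Whitney test, if wanted, as a labelled sensitivity analysis with no non-inferiority decision attached. The same sentence supplies the margin rule that section 6 lacks for the t-test.

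The cost is one sentence, and this change alone requires no new sample size. The statistical price is some power under heavy skew: about 80% for Welch against 89% for the shifted rank test at the planned 2.2-day advantage, with 16 per group and skewness −1.5. That comparison flatters the rank test, because in the same setting it also passes too often at the margin. Welch lessens the drift under skew but does not fully remove it.

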**Figure 4 fig4:**
[figure not shown]
Placement of NIRS.

**Table 1 tab1:** Study schedule.

Stage	Baseline	Treatment			Follow-up (after treatment)		
Time point	Day 0	Day 1	→	Day 28	Day 28	→	Day 168
Enrolment							
Eligibility	×						
Informed consent	×						
Allocation	×						
Interventions							
FSN		×					
Flunarizine hydrochloride		×					
Assessment							
MMD	×			×	×	×	×
MSQOL scores	×			×	×	×	×
VAS scores	×			×	×	×	×
MIDAS scores	×			×	×	×	×
Headache diaries	×			×	×	×	×
NIRS		4 measurements					
Adverse events	×	×					

Fu’s Subcutaneous Needling (FSN), developed by [name], is a novel acupuncture technique derived from traditional Chinese medicine and grounded in anatomy, physiology, and myofascial trigger point theory. It involves repetitive sweeping of the subcutaneous loose connective tissue over pathologically tense muscles to reduce peripheral muscle tension (19), combined with resistance exercises to promote tissue reperfusion. This approach rapidly alleviates muscle ischemia and hypoxia (20), reduces mechanical compression on surrounding tissues, and demonstrates notable efficacy in pain management (21, 22).

Currently, there is a paucity of clinical studies on the application of floating acupuncture for MWoA, and objective assessments of its therapeutic effects are lacking. Therefore, we propose a randomized controlled trial to assess the clinical efficacy and underlying mechanisms of FSN in treating MWoA, with the goal of identifying safer and more effective treatment strategies. We hypothesize that floating acupuncture is non-inferior to flunarizine hydrochloride in alleviating pain intensity, reducing attack frequency, and enhancing quality of life in MWoA patients.

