#### Inclusion criteria

2.3.1

Meeting the diagnostic criteria for migraine without aura (MwoA) according to the International Classification of Headache Disorders, 3rd edition (ICHD-3) (1);Aged 18–65 years;A history of migraine for at least 1 year;At least 2 migraine attacks per month (meet the diagnostic criteria for migraine without aura (criteria B–D) as defined by ICHD-3);No prophylactic medications or other treatments for migraine within the past month;Visual Analog Scale (VAS) score >3;Voluntarily provided written informed consent.

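### The within-arm before/after tests of MMD, MSQOL, MIDAS and VAS test for change over time, not for a treatment effect, and should be replaced by per-arm changes labelled descriptive

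*Protocol article*

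**What the plan says.** Section 6 (Statistical analysis) of the protocol article plans two kinds of test on the same four clinical outcomes: MMD, MSQOL, MIDAS and VAS.

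- Between arms: "between-group differences in changes from baseline to 4 weeks post-treatment are analyzed using either the independent" t-test or the Mann–Whitney U test.
- Within each arm: "Intra-group comparisons between baseline and 4-week post-treatment measurements are conducted using paired *t*-test or Wilcoxon signed-rank test".

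One rule covers both: "All tests employ two-sided comparisons, with statistical significance defined as" p < 0.05. Section 6 calls the repeated-measures ANOVA supplementary. It gives the within-arm tests no such label and does not say what they are for.

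Three features of the design bear on how they can be read:

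- Section 2.3.1 sets entry thresholds, among them "Visual Analog Scale (VAS) score >3" and a minimum of two attacks per month.
- Section 2.2 has two active arms and no other, with patients "randomly assigned in a 1:1 ratio to receive either FSN treatment (*n* = 22) or pharmacological treatment (*n* = 22) for 4 weeks".
- Section 2.5 says that neither participants nor practitioners are blinded.

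The aim is worded in two ways. The Introduction says that "we propose a randomized controlled trial to assess the clinical efficacy and underlying mechanisms of FSN in treating MWoA", and then gives the hypothesis as non-inferiority to flunarizine. The Conclusion repeats the non-inferiority hypothesis.

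**The concern.** A paired t-test or Wilcoxon signed-rank test within one arm asks whether the outcome moved between baseline and week 4. Whether the treatment moved it is a different question. In this trial at least three things could lower the scores without any specific effect of FSN: regression to the mean after entry on a symptom threshold, the natural course of migraine, and expectation in patients who know their treatment and report their own outcomes. Nothing within a single arm separates these from a treatment effect, and there is no sham or untreated arm to do so.

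Two misreadings are at stake. The first is that a significant fall in the FSN arm shows that FSN works. Among the clinical tests listed in section 6, only the within-arm tests look at FSN alone, so they are the natural place to seek support for an absolute claim. The second is that a significant result in one arm beside a non-significant one in the other shows a difference between arms.

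A related pattern would be a significant fall in both arms with no significant difference between them. That shows neither efficacy nor non-inferiority, and section 6 does not mention the 1-day margin of section 2.4 that would settle the second question.

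**Working it through.** The document gives no error rate or power for the within-arm tests, so there is no stated figure to reproduce. The check asks how often the paired t-test on MMD would be significant if FSN had no specific effect but MMD fell for other reasons.

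**Inputs**

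- Section 2.4: "the MMD in the flunarizine hydrochloride group decreased by 1.9 ± 2.3 from baseline". The same section quotes a fall of 4.1 ± 3.5 for the acupuncture arm of the referenced trial. The SDs of change are therefore 2.3 and 3.5; 3.5 is the closer one for a needling arm.
- Sections 2.2 and 2.4: 22 per arm, with 25% dropout anticipated. 22 × 0.75 = 16.5, so about 16 completers per arm.
- Section 6: two-sided 0.05.
- Assumption: a share s of the 1.9-day fall is non-specific. The document gives no share, so s = 25%, 50%, 75% and 100% are shown. The mean falls are 1.9 × s = 0.475, 0.95, 1.425 and 1.9 days.
- Assumption: normally distributed changes.

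**Formula**

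Noncentrality δ = fall / (SD/√n), with n − 1 degrees of freedom. The chance of significance is P(|T| > t₀.₉₇₅), where T is noncentral t. The critical value is 2.080 at n = 22 and 2.131 at n = 16.

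Example: SD 3.5, n = 22, s = 50%. The standard error is 3.5/√22 = 0.746, δ = 0.95/0.746 = 1.27, and the chance is 23%.

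**Chance of p < 0.05 within an arm with no specific effect**

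| SD | n | 25% | 50% | 75% | 100% |
|---|---|---|---|---|---|
| 3.5 | 22 | 9% | 23% | 45% | 68% |
| 3.5 | 16 | 8% | 17% | 33% | 53% |
| 2.3 | 22 | 15% | 46% | 79% | 96% |
| 2.3 | 16 | 12% | 34% | 64% | 87% |

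With no change over time the chance is 5% throughout.

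**Exactly one of two identical arms significant**

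If each arm is significant with probability p, this happens with probability 2p(1 − p). The reference value with no change over time is 2 × 0.05 × 0.95 = 9.5%. For SD 2.3 and n = 22 the results are 26%, 50%, 33% and 8% for the four shares. The last lies below the reference because both arms are then nearly always significant.

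**The between-arm test in the same setting**

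Both arms were given the same mean fall (1, 1.5 or 1.9 days), with SDs 3.5 and 2.3 and n = 16 or 22, in 40,000 simulated trials each. The independent t-test on change was significant in 4.8% to 5.3%. Randomisation removes the shared change, so this test holds its level.

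**The case against.** The strongest defence is that the document never uses the within-arm tests as evidence of efficacy. The hypothesis is comparative, the sample size rests on a between-arm difference, the Discussion describes a comparison with flunarizine, and section 6 lists the between-arm test first. This stands. A reader might infer that the plan replaces the randomised comparison with before/after tests, or offers them as proof that FSN works. The text supports neither reading: the between-arm test is planned on the same four outcomes and is undamaged, and no sentence gives the paired tests that role.

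It is also correct that each paired test keeps its 5% level for its own null. The percentages above become false positives only if a reader takes the result as a statement about treatment. They depend on an assumed share: at the low end, with SD 3.5, the rate is only 8% to 9%. The document does not support saying that such results will be frequent, only that they could be.

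Finally, the labelling of supportive tests is often left to a full protocol or analysis plan, and neither is shown. That carries less weight here. The article does state these tests, puts them under the same significance rule as the between-arm tests, and uses the label supplementary for the ANOVA but not for them.

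**Conclusion.** The point holds in a limited form. The within-arm tests answer a question about change over time that does not bear on the trial's comparative hypothesis. In this design their significance cannot be attributed to FSN, nor can a contrast of significance between arms be read as a difference. This rests on the stated design and needs no assumed figure.

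The size of the risk does need one. If a quarter to all of the quoted 1.9-day fall is non-specific, an FSN arm without specific effect gives p < 0.05 on MMD in 9% to 68% of trials at n = 22 and 8% to 53% at n = 16, using SD 3.5. With SD 2.3 the ranges are 15% to 96% and 12% to 87%. The calculation covers MMD only, because the document gives no means or SDs for the other three outcomes.

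The primary comparison and the sample size are untouched by this point. It is a weakness in what will be reported beside the comparison, worth correcting because the correction is so small.

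**What to change.** In section 6, replace the sentence on within-arm tests with two statements:

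- Change from baseline to week 4 in MMD, MSQOL, MIDAS and VAS is summarised per arm as mean (or median) change with a 95% CI, for description only and without p-values.
- Conclusions on efficacy rest on the between-arm difference in change with its CI; for MMD that interval is judged against the 1-day margin of section 2.4.

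The cost is a short edit to one section. No patients, visits, measurements or data items change, and the size of the change in each arm is still reported. What is lost is a set of within-arm p-values.
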